#### Process evaluation: semi-structured interviews

A process evaluation will be conducted after completion of the data collection. Qualitative data will be collected from approximately five telephone interviews with representatives of the participating supermarket and ten interviews with participants from both arms. Participants will be asked whether they are willing to be part of the process evaluation at recruitment, and those that take part will be provided with a £10 voucher. Recruitment of the supermarket staff to the telephone interviews will be via direct contact with key staff with input to the project. The telephone interviews will be semi-structured and will probe for information about the mechanism of delivery of the intervention, data collection, data transfer, acceptability of the interventions, and feasibility of rolling out the study design to a full trial. The interviews will be digitally recorded and transcribed.

#### Process evaluation: web analytics

The use of web analytics to track how people interact with web-based health interventions has been demonstrated to be a worthwhile contribution to process evaluations, providing quantitative data alongside the qualitative data collected by the semi-structured interviews [25]. We will use a combination of Piwik analytics (http://piwik.org/) or a similar package, and custom built analytics tools, which will allow us to link visits to the intervention website to unique participant id codes. The analytics package will be used to measure the following variables for each participant:The number of visits to the intervention website,The number of visits to each webpage within the intervention,The average length of time spent visiting the website,Completion of the intervention (i.e. whether all of the sections of the intervention are visited across all visits),Responses to the experiential task (i.e. whether the participant gets the correct or incorrect answer in the experiential task),The internet browser and operating system used by the participant (this will allow us to identify the proportion of participants visiting the intervention on a smart phone or handheld device),Pathway used by participant (i.e. how they navigated the website),The time and date of each visit.

These data will be used to analyse how the participants engaged with the different elements of the intervention and to identify potential areas of improvement, both in terms of content and structure.

### Statistical analysis

Demographic characteristics and outcomes data will be summarised with counts and percentages for categorical variables, means (standard deviations) for normally distributed continuous variables and medians (with interquartile or simple ranges) for other continuous variables. At time points T1 and T2, repeated measures ANCOVA will be used to assess differences between intervention and control arms, adjusted for gender, dependent children and baseline measures [26]. If outcome data are not normally distributed, then differences will be assessed either using transformed data or by using appropriate non-parametric tests. Results will be presented as point estimates accompanied by 95 % confidence intervals. Analyses will be conducted on an ‘intention to treat’ basis (i.e. data for participants who unsubscribe from the study will be used in the final analyses). Subgroup analyses by socioeconomic status will be conducted to assess potential impact of the intervention on social inequalities. Since this is a pilot study with a sample size based on a small effect size and unclear recruitment rates, it is not guaranteed that the study will be adequately powered to detect differences between intervention and control arms, particularly in sub-analyses. The socioeconomic status of the participants will be compared with that of the loyalty card database from which they are drawn to assess inequalities in recruitment, using area-level deprivation measures.

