## Methods/design

The design is a two-arm parallel randomised controlled trial comparing the intervention against information about traffic light labelling. Data collection will take place over 44 weeks, with 26 weeks of baseline data (−T1), 6 weeks of intervention (T1) and 12 weeks of follow-up without intervention (T2), with questionnaire data collected at recruitment (T0) and during the intervention (T1) and follow-up (T2) periods. Figure 2 shows how the trial will progress, and Table 2 gives a timetable for data collection.

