#### Effect sizes

The research team will receive electronic sales data for all food purchases during the study period from the participating supermarket at two stages: after allocation and after completion of the study. The primary outcome measures for the main trial will be healthiness of ready meals and pizzas that carry traffic light labelling. For each participant, mean healthiness of all ready meals and pizzas purchased during the entire time period will be assessed in T-1, T1 and T2 and differences between intervention and control arms at T1 and T2 will be controlled for differences at baseline (T-1). Purchase data will be collected via electronic sales data linked to participants’ loyalty cards. Comparisons between intervention and control at T1 will measure the immediate effect of the intervention, and at T2 will measure whether the effect is sustained for the following 12 weeks after the intervention is removed. The ‘healthiness’ of each purchased ready meal or pizza will be a combination of the information provided on the traffic light label, weighted by factors derived from a parallel choice experiment assessing the importance of different elements of the label (manuscript under preparation). Details of how the scale is constructed are provided in the appendix.

Secondary outcome measures (assessed as difference in means and SD between intervention and control) will beNumber of ready meals and pizzas purchased in T2/T1.Amount (£) of ready meals and pizzas purchased in T2/T1.Total amount (g) of fat, saturated fat, sugar and salt in ready meals purchased in T2/T1.Amount (£) of all foods purchased in T2/T1.Amount (£) of fruit and vegetables purchased in T2/T1.Psychosocial variables including beliefs, attitudes, intention, outcome expectancies and procedural knowledge measured in T2/T1.

Secondary outcome measure 3, in combination with the primary outcome measures, will allow us to calculate clinically meaningful minimum differences for a sample size calculation for a full trial.

The data collected from the loyalty cards and the questionnaires will be stored in an anonymised dataset held on servers owned and maintained by the study sponsor for a period of 15 years, after which all datasets will be deleted.

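### Secondary purchase outcomes 1 to 5 are totals over windows of unequal length (26, 6 and 12 weeks), so T1 and T2 effects in one repeated measures ANCOVA are not on the same scale

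*Protocol article*

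**What the plan says.** Methods/design and Table 2 set three windows: a 26-week baseline, then "6 weeks of intervention (T1) and 12 weeks of follow-up without intervention (T2".

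Outcome measures, Effect sizes, makes the primary outcome a per-item average: "mean healthiness of all ready meals and pizzas purchased during the entire time period will be assessed in T-1, T1 and T2". The first five secondary outcomes are instead accumulated quantities: the number of ready meals and pizzas, the money spent on them, "Total amount (g) of fat, saturated fat, sugar and salt in ready meals purchased in T2/T1", spending on fruit and vegetables, and "Amount (£) of all foods purchased in T2/T1". None carries a time unit. The sixth is a set of questionnaire scores.

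The Statistical analysis section gives one method for all outcomes: "At time points T1 and T2, repeated measures ANCOVA will be used to assess differences between intervention and control arms". The covariates are the two stratification factors and the baseline value. It does not say whether T1 and T2 share an error variance or a baseline slope.

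On the purpose of the second window, Effect sizes says that the comparison "at T2 will measure whether the effect is sustained for the following 12 weeks after the intervention is removed".

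**The concern.** A repeated measures model is easy to read when its occasions measure the same quantity on the same scale. A 6-week total and a 12-week total do not. A steady change in weekly buying looks as if it doubles once the website closes, and an effect that halves looks perfectly maintained.

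The stake is what the pilot hands on. Study objectives asks for effect sizes as mean and SD for the secondary outcomes, and Effect sizes says that outcome 3, with the primary outcome, will help set the minimum meaningful difference for the main trial. A mean and SD tied to one window length serve that purpose only if the main trial keeps the same windows. H2 concerns how many items people typically buy, which is naturally a rate. Under Consent, sales data of withdrawers are cut off at withdrawal, so their totals also cover fewer weeks than everyone else's.

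**Working it through.** **Plan's own figures.** No figure in the article addresses this point. The stated detectable effects do reproduce, assuming two-sided 5 %, 80 % power and 1:1 allocation: (1.960 + 0.842) × √(2/600) = 0.162 for 1200 data sets (stated 0.16), and 2.802 × √(2/200) = 0.280 for 400 (stated 0.28). This point does not change them.

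**Step 1: size of the effect.** Inputs: window lengths of 6 and 12 weeks (Methods/design). For a constant effect δ per week:
- T1 difference = 6δ; T2 difference = 12δ; ratio 12/6 = 2.0. This needs no assumption beyond untransformed totals.
- If the weekly effect halves in T2, the T2 difference is 12 × δ/2 = 6δ, the same as at T1.
- Averaging the two totals gives (6δ₁ + 12δ₂)/2 = 3δ₁ + 6δ₂, so T2's weekly effect has twice the weight of T1's.
- Example: a 10 % cut from an assumed 1 item per week is −0.6 items at T1 and −1.2 at T2.

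**Step 2: spread of the totals.** Let B be the between-person and W the within-person weekly variance, with B + W = 1. A total over w weeks has variance w²B + wW. The documents do not give B, so its full range is shown. If one variance is pooled, P = (V1 + V2)/2, and coverage at each window is 2Φ(1.96 × √(P/V)) − 1.

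| B | V1 (6 wk) | V2 (12 wk) | V2/V1 | Pooled coverage T1 | Pooled coverage T2 |
|---|---|---|---|---|---|
| 0 | 6 | 12 | 2.00 | 98.4 % | 91.0 % |
| 0.3 | 15.0 | 51.6 | 3.44 | 99.7 % | 88.5 % |
| 1 | 36 | 144 | 4.00 | 99.8 % | 87.9 % |

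In SD units the T2/T1 effect ratio is 2/√(V2/V1), which runs from 1.41 down to 1.00. The doubling is therefore a feature of raw units.

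**Step 3: baseline covariate.** The slope of a w-week total on the 26-week baseline total is wB/(26B + W), so the T2 slope is twice the T1 slope whatever B is. One common slope would fit neither window.

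**Step 4: simulation, 1200 participants, 2000 runs.**
- Normal weekly data, B = 0.3, constant effect 0.1 per week, baseline total as covariate: estimates 0.60 (T1) and 1.20 (T2); residual variance ratio 2.36. Coverage is 99.1 % and 89.2 % with pooled variance, and 94.4 % and 94.6 % with separate variances. A T2-minus-T1 test of the arm difference rejects in 80 % of runs on totals and 6 % per week, although the weekly effect never changes.
- Skewed counts (Poisson purchases, 0.5 or 1 item per week, between-person CV 0.7, period CV 0.3), constant 10 % reduction: the same test rejects in 24 to 29 % of runs on totals and about 5 % per week. Pooled coverage is 99 % at T1 and 89 to 90 % at T2.

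**Step 5: primary outcome.** A per-item mean does not grow with window length, so there is no doubling. If purchases are proportional to weeks, V2/V1 lies between 0.5 and 1, and pooling would put T1 coverage between 91 and 95 %.

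**The case against.** The best defence has four parts.

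- **Transformation.** The Statistical analysis section allows transformed data or non-parametric tests if outcomes are not normal, and purchase counts usually are not. On log(x + 1), the 1-item-per-week setting with a 10 % reduction gives −0.084 at T1 and −0.095 at T2, and the T2-minus-T1 test rejects in 5.4 % of runs (29 % raw). At 0.5 item per week it rejects in 7.0 % (24 % raw). This stands in part. The log route largely removes the doubling, but it is conditional and only one of two options. It also leaves untransformed means and SDs for the main trial on unequal windows.
- **Error structure.** A reader might infer that the T1 and T2 confidence intervals are wrong. The documents do not support that: neither a pooled variance nor a common slope is stated, and covariance structure is normal content for an analysis plan that is not shown. This stands, so coverage can be stated only conditionally.
- **No arm-by-time test is planned.** A reader might infer that the trial will report a growing effect. The article plans arm comparisons at T1 and at T2, each unbiased, and its remark on sustained effect sits in the paragraph on the primary outcome. This stands. The rejection rates above show the distortion; they are not the error rate of a planned test. The secondary outcomes are nevertheless estimated in the same two windows, which invites the comparison.
- **Any reader can divide by weeks.** That is true of the mean difference. It does not repair an average over both windows, a common baseline slope or censored totals, and an SD does not scale in proportion to weeks.

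**Conclusion.** The point holds for secondary purchase outcomes 1 to 5, including the gram totals of outcome 3. On untransformed totals a constant weekly effect is twice as large at T2 as at T1. Any T1-versus-T2 reading, or any average of the two, is confounded with window length. This rests only on the stated windows and on the outcomes being totals as written.

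It does not follow that the arm comparison within either window is biased, or that the primary score or questionnaire scores are affected by the doubling. H2 and H3 are not put at risk by the pilot itself, since the article reserves the hypotheses for the full trial.

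The interval problem is conditional. If one variance is pooled, coverage on totals is about 99 % at T1 and 88 to 91 % at T2, under assumed rates and variances. With period-specific variances it is nominal.

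T2/T1 most likely means both periods. Read literally as a ratio, a constant proportional effect would cancel out, so the notation needs correcting either way. This should be changed, because the pilot's estimates are meant to feed the main trial's design.

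**What to change.** 1. Define secondary outcomes 1 to 5 as number, pounds or grams per week of observed time in all three windows, and use the per-week baseline value as covariate. For withdrawers, observed time ends at the withdrawal date.
2. For all outcomes, estimate the T1 and T2 arm differences with period-specific baseline slope and residual variance. Use either one ANCOVA per period, or one model with arm × time, baseline × time and an unstructured covariance.
3. Report the per-week SD for each window together with its length. The SD of a weekly average, √(B + W/w), still depends on w, and the main trial's planners need to know which window it came from.
4. Replace T2/T1 in the outcome list by: at T1 and at T2.

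The cost is a change of outcome definitions and model wording. The data, software and sample size stay the same.

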All participants will be asked to complete two further psychosocial questionnaires similar to that used at T0. A link to the questionnaires will be emailed at the end of the intervention period (T1) and directly after completion of the follow-up period (T2). Participants will receive a £10 electronic gift voucher (that cannot be used in the participating supermarket) for completing the questionnaire at T1 and a further £10 electronic gift voucher for completing the questionnaire at T2. Four reminder emails will be sent to all participants throughout the course of the trial. The first two reminder emails will be sent during T1 (in weeks 3 and 5) reminding all participants to use their loyalty card for food purchases, directing the control arm to information about traffic light labels and directing the intervention arm to the intervention. The remaining two emails will be sent a week after the follow-up psychological questionnaires are sent out, in order to remind participants to complete them.

Measuring recruitment, retention and data completion rates is an objective of the study—for the purpose of recruiting for the pilot trial, we are assuming the following:Recruitment rate of 5 %—based on recruitment for a previous study using the same method and population which had a recruitment rate of 3.8 % (manuscript under preparation), adjusted for web-based recruitment with incentives [20].Loss of 20 % of consenting participants due to failure to meet eligibility criteria 5, 6 or 7 (estimate to be refined from pilot data).Retention rate of 93 %—based on retention rates for the SHOP trial, which collected 6 months of electronic supermarket sales data [21].Questionnaire data completion rate of 30 %—based on a 25 % completion rate for follow-up of web-based questionnaires [22] adjusted for web-based retention with incentives [20].

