We are aiming to receive approximately 400 complete sets of psychosocial questionnaire data and 1200 complete sets of electronic sales data. This will allow us to detect an effect size (measured by Cohen’s d statistic) of 0.28 for the psychosocial questionnaire data and 0.16 for the electronic sales data. In general, effect sizes of 0.2 or less are considered ‘small’. The data collected in the pilot trial will allow us to refine our sample size estimates for the main trial. According to the assumed rates detailed above, we will recruit approximately 1300 participants, which will require us to email 33,000 loyalty card holders, from a total database of over 1 million. Should recruitment rates be lower than expected, further recruitment emails will be sent out.

Each of these assumed rates will be tested in the pilot trial, and the recruitment strategy may not result in the estimated number of participants. For example, it is not clear whether UK supermarket shoppers consistently use loyalty cards as much as in New Zealand, where the estimate of retention rate originates.

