### Consent

All participants will complete an online consent form before being included in the study, which will be accessible from the website link in the recruitment email. All potential participants will have to review a participant information sheet before enrolling, indicating the nature of the study and the implications of participation. Participants will be informed that they may withdraw or unsubscribe from the study at any point without giving a reason. Unsubscribed participants will receive no further contact from the study team, but food purchase data will continue to be collected. Those participants who withdraw will receive no further contact and electronic sales data will be censored at the withdrawal date. Participants will express their desire to withdraw or unsubscribe by calling a UK landline during office hours or by contacting a dedicated email address.

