### Outcome measures

#### Recruitment, retention and data completeness

Participants will be deemed to have been fully retained in the study if (a) they do not contact the study team to withdraw or unsubscribe and (b) if psychosocial questionnaires sent at T1 and T2 are completed. Partial retention rates for those who only complete the questionnaire at T1 or who only contribute food purchase data will also be calculated. Recruitment and retention rates from different socioeconomic groups (measured by area-level deprivation) will be assessed by comparison of the socioeconomic profile of the recruited sample with the profile of the whole loyalty card database from which the sample was drawn.

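### For the psychosocial questionnaires, repeated measures ANCOVA makes poor use of participants who answer only one follow-up wave; a likelihood-based mixed model would keep them

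*Protocol article*

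**What the plan says.** All places are in the protocol article.

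- **Method.** Statistical analysis, for both follow-up waves: "repeated measures ANCOVA will be used to assess differences between intervention and control arms". One method is named for all outcomes, and the psychosocial variables are among the secondary outcomes listed under Effect sizes. The comparison takes account of the two stratification factors and the baseline value, which for these variables is the T0 questionnaire.
- **Expected response.** Recruitment and allocation strategy: "Questionnaire data completion rate of 30" per cent.
- **Target.** Same section: "We are aiming to receive approximately 400 complete sets of psychosocial questionnaire data and 1200 complete sets of electronic sales data". The detectable effect sizes given there are d = 0.28 for questionnaires and 0.16 for sales data.
- **Partial responders.** Recruitment, retention and data completeness: "Partial retention rates for those who only complete the questionnaire at T1 or who only contribute food purchase data will also be calculated". The text does not say whether these people enter the effect analysis.

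**The concern.** A classical repeated measures ANCOVA needs the outcome at every wave. Fitted jointly over T1 and T2, it loses each participant who lacks one of the two questionnaires. That fits poorly with an outcome for which the plan expects about 70 % of participants not to supply a complete set.

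The T1-only group may not be small. The T2 questionnaire follows the T1 questionnaire by 12 weeks, and each carries its own £10 voucher, so a participant can answer the first and skip the second.

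The third study objective is to estimate the mean and SD of effects on these psychosocial variables. They are also the outcomes that bear on H4, to be tested in the full trial. Two things are at stake: precision that the collected data could provide, and bias if those who drop out between T1 and T2 differ by arm in their T1 answers.

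**Working it through.** **Inputs.** From the article: 1300 recruited, 30 % questionnaire completion, d = 0.28 for about 400 sets. Assumed, because not stated: two-sided alpha 0.05, power 80 %, 1:1 allocation. These values reproduce the article's figures. A complete set is read as having both T1 and T2. The number answering at T1 only is not given, so a range is shown.

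**Step 1: the plan's own figure.** With SD = 1 and N in total,

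d = (1.960 + 0.842) × √(4/N) = 5.603/√N.

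At N = 400, d = 0.280, as stated. From the rates, 1300 × 0.30 = 390 (d = 0.284), which agrees with approximately 400.

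**Step 2: T1 effect.** Suppose 390 answer both waves and a larger share answers at T1. A joint classical fit uses the 390. A model that uses all available answers has the larger N at T1.

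| Assumed T1 response | N at T1 | T1-only | Detectable d at T1 |
|---|---|---|---|
| 30 % | 390 | 0 | 0.284 |
| 35 % | 455 | 65 | 0.263 |
| 40 % | 520 | 130 | 0.246 |
| 50 % | 650 | 260 | 0.220 |
| 60 % | 780 | 390 | 0.201 |

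Baseline adjustment would shrink every row by the same factor, so the comparison stands.

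**Step 3: T2 effect.** Suppose everyone who answers at T2 also answered at T1. Let ρ be the T1-T2 correlation given baseline, and N1 the number at T1. The likelihood estimate then has

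effective N at T2 = 390 / [1 − ρ²(1 − 390/N1)].

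| Assumed T1 response | ρ = 0.5: effective N (d) | ρ = 0.7: effective N (d) |
|---|---|---|
| 35 % | 404 (0.279) | 419 (0.274) |
| 40 % | 416 (0.275) | 444 (0.266) |
| 50 % | 433 (0.269) | 485 (0.254) |
| 60 % | 446 (0.265) | 517 (0.247) |

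Both forms of ANCOVA, joint or per wave, stay at 390 for T2.

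**Step 4: illustrative simulation.** N = 1300, true effect 0.28 at both waves, 50 % answering T1 at random, about 30 % answering both, correlation with baseline 0.5, T1-T2 correlation 0.6, 2000 replicates.

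- *T2 dropout unrelated to outcome.* Both approaches are unbiased. The standard error at T1 is 0.084 for complete sets and 0.066 with all data, a variance ratio of (0.084/0.066)² = 1.62. At T2 it is 0.086 and 0.082.
- *T2 dropout dependent on the T1 score, in opposite directions by arm* (log-odds ±0.5 per SD, a deliberately adverse choice). Complete sets give 0.56 at T1 and 0.41 at T2; the likelihood approach gives 0.28 at both. A separate ANCOVA at T1 would also give 0.28 there, but a separate ANCOVA at T2 uses the same participants as the complete sets and gives 0.41.

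The adverse case shows the direction of the risk. It does not predict its size.

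**The case against.** The strongest objection is that the analysis section never limits itself to complete sets. The phrase "approximately 400 complete sets of psychosocial questionnaire data" is a target for data received. The wording about time points can be read as one ANCOVA per wave, and Effect sizes describes the purchase comparisons at T1 and T2 as answering different questions. On that reading T1-only responders stay in the T1 comparison. This stands: exclusion at T1 follows only from a joint classical fit. But the per-wave reading still leaves their T1 answers out of the T2 estimate, so the method can be improved either way.

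It can also be said that missing-data handling belongs in an analysis plan not shown. That is right for imputation or weighting, and their absence is no fault. The point here concerns the method that the article does name.

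Thirdly, if response depends only on T0 score, arm and strata, a correctly specified baseline-adjusted ANCOVA is already valid. That is also true. The bias argument applies only where T2 response depends on T1 answers.

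Four stronger readings are tempting, and the documents do not support them:

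- *That everyone's T0 answers are thrown away.* T0 scores of those analysed are the baseline covariate. Only non-responders' T0 scores go unused, and they add almost nothing to a baseline-adjusted contrast.
- *That the 400 should be 1300 × 0.93 × 0.30 = 363.* The 93 % comes from a trial of sales data. The article lists it separately from the questionnaire rate, which would ordinarily already count leavers as non-completers.
- *That the intention-to-treat statement is empty for questionnaires*, because "Unsubscribed participants will receive no further contact from the study team". Someone who unsubscribes after T1 has already given T0 and T1 answers, and these can be used.
- *That a bias from unequal response by arm can be quantified.* The article gives no response rates by arm and no link between response and outcome. A missing-at-random model would not in general remove selection on unobserved outcomes.

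**Conclusion.** The point holds in limited form. For the psychosocial outcomes, the named method suits the expected pattern of response poorly. In a joint fit it drops one-wave responders; fitted wave by wave, it ignores T1-only responders' T1 answers at T2.

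If 30 % answer both waves and 35-60 % answer at T1, the detectable d at T1 falls from 0.28 to about 0.26-0.20 relative to a joint fit. Relative to separate fits there is no T1 gain. At T2 it falls from 0.28 to about 0.28-0.25 for correlations of 0.5 to 0.7, negligible at the low end. These sizes rest on the assumed T1 response, the correlation, and conventional alpha and power.

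Severity is low. The outcomes are secondary, the trial is a pilot, completion is itself something it sets out to measure, and the article warns that power is not guaranteed.

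**What to change.** For the psychosocial outcomes, replace repeated measures ANCOVA with a likelihood-based mixed model for the T1 and T2 scores. Include arm, time, arm-by-time, the T0 score, gender and dependent children. State that every participant with a T1 or T2 questionnaire is included, and report the arm difference at each wave.

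Add a sensitivity analysis for non-response, by weighting or multiple imputation, using T0 answers, area deprivation and purchase data. This is where non-responders' T0 answers are useful. The figure of about 400 complete sets can stay.

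The cost is a few sentences and modest programming, with no new data. The downside is reliance on missing at random, though that is a weaker assumption than a complete-case analysis needs.
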